## Abstract

**Background:**

Although the benefits of physical activity (PA) on health are recognised, prostate cancer patients do not follow PA recommendations. The barriers to PA, whether physical, environmental or organisational, are known. Furthermore, even when such barriers are overcome, this achievement is not systematically accompanied by a change in lifestyle habits. The proposal of a programme enabling the integration of PA in the patient’s everyday life represents a new challenge in the personalized management of cancer patients. Peer-mentoring interventions have demonstrated their effectiveness in increasing adherence to PA by patients. This study aimed (1) to assess the feasibility of a peer-mentoring intervention: the Acti-Pair program in a local context and (2) to assess the effectiveness of the intervention in this context.

**Methods and analysis:**

A pre-post  design pilot study will be used to evaluate feasibility, potential effectiveness and implementation outcomes overs in prostate cancer patients. We performed a mixed quantitative and qualitative prospective study to assess means and process indicators and the implementation of the Acti-Pair program. This study will be performed in cancer centres of Loire district and will be comprised of three successive stages (1) diagnosis of the target population, (2) recruitment and training of peers, and (3) implementation of this intervention in the Loire department.

**Discussion:**

This study will allow us to extend the peer-mentoring intervention to other contexts and assess the effectiveness of this intervention and its generalisability.

**Supplementary Information:**

The online version contains supplementary material available at 10.1186/s40814-022-00966-9.

## Background

Prostate cancer is the most common male cancer in France (50,413 new cases per year in 2015) [1] and in Europe (365,000 new cases per year estimated in 2015) (https://ec.europa.eu/jrc/en/publication/epidemiology-prostate-cancer-europe). Recognised benefits of physical activity (PA) in tertiary prevention of prostate cancer include maintenance of autonomy, increased quality of life, and prolonged life expectancy [2, 3]. The beneficial role of PA regarding morbidity and mortality has already been demonstrated for patients with prostate cancer [4, 5]. Aerobic exercise may reduce prostate cancer progression and prostate cancer-specific death by influencing energy metabolism, inflammation, oxidative stress, and androgen receptor signalling pathways [6]. Accumulating evidence from prospective cohort studies suggests that PA, specifically moderate-to-vigorous physical activity (MVPA; i.e. activities that require an energy expenditure ≥ 3 times the resting metabolic rate, such as brisk walking or cycling), is associated with reduced risks of advanced, aggressive, and fatal prostate cancer [6]. Respect of new health standards (i.e. regular PA practice, diet, stress management, etc.) and lifestyle changes can be beneficial, even after 60 years of age [7]. Sedentary lifestyles, regardless of physical inactivity, increase the incidence of various cancers (breast, colorectal, endometrial and ovarian) and the risk of cancer-related mortality [8].

Given the strength of evidence, the promotion of PA and the fight against the sedentary lifestyle for people with chronic diseases is included in several national plans and programmes in France (National Nutrition and Health Programme 2011–2015 [9], National Health Strategy 2018–2022 [10], Cancer Plan 2014–2019) [11]. The World Health Organization (WHO) [12] recommends practicing 150 min of moderate intensity endurance activity (equivalent to brisk walking) per week. However, simply providing information about the benefits of this practice is not enough to change patients’ lifestyles.

Strengthening patients’ adherence to advice on PA in tertiary prevention is a challenge for personalised cancer care. The objective does not aim solely to treat cancer pathology but also to consider the patient as a whole, including all aspects of the patient’s life (including family, leisure and work activities), taking into account the person’s lifestyle in general with the objective of achieving a better quality of life. Although the benefits of PA on health are recognised, studies have shown that 60–70% of prostate cancer patients do not follow PA recommendations [13, 14]. It is recognised that prostate cancer patients are less adherent to PA practice recommendations than breast cancer patients [13, 14]. The identified barriers to the practice of regular PA by patients with prostate cancer are the following:Physical [15, 16] decline related to age or comorbidities, symptoms of the disease, undesirable side effects of the treatments, fatigue painPsychological: personal efficacy, self-determination [17], former practice of PA, timing of the proposal given for PA following diagnosis [18], recommendations of PA by the oncologist [19], social support [20]Organisational: climatic conditions, temporal, geographical, or financial constraints [21].

These barriers partly explain the lack of PA in prostate cancer patients. However, overcoming these barriers is not systematically accompanied by a change towards a more active lifestyle. Encouraging people to participate in regular PA against the background of an inactive lifestyle is difficult, requiring attention to important psychosocial and behavioural influences [18, 22]. A major challenge is to provide a support structure for PA until this becomes a pattern of sustained healthy behaviour [23].

Peer-mentoring intervention helps survivors of pathological conditions to become physically active [24]. Peer mentors are individuals with similar salient characteristics, who have acquired experiential knowledge and are willing to share this [24]. Trinh et al. showed that a supervised 12-week PA programme continued to have motivational effects 5 years after the program had ended, including the perception of peer commitment [25]. Rabin et al. underlined the need for obtaining support from other patients who can understand their reactions to cancer [20]. Through the intervention of a peer, patients can rely on the support of a social environment and thus overcome the various psychological barriers identified in the literature (loss of self-esteem, lack of motivation, and competence) [26]. Peer-mentoring interventions have demonstrated their effectiveness in increasing adherence to MVPA by patients with diabetes [27], in older adults [28, 29], and more recently with breast cancer [30, 31] and prostate cancer patients [32]. They have also shown their effectiveness in promoting adherence to PA and long-term maintenance of PA by cancer patients [30, 31].

We hypothesised that an intervention combining three components helps to initiate and maintain in “real life” a behavioural change in prostate cancer patients with regard to the regular practice of PA:Involving a peer mentor whose role is to provide social and motivational support by sharing his personal experience of the disease, its treatments, and the practice of PA with another patient.Building a personalised and realistic PA project according to the patient’s needs, constraints, preferences, and environment. Evidence has shown that empowering patients to make their own choice as to which activity they intend to practice and where and with whom they will practice can improve PA level [33].Benefitting from close support by healthcare professionals within the framework of a prescription for PA, as well as by PA professionals.

The available literature suggests that it is important to set up an intervention to promote and integrate PA in “real life” [34]. Rabin et al. specified the importance of flexibility in the implementation of PA programmes [20].

The primary objective of this pilot study will be to assess the feasibility, potential effectiveness and implementation of Acti-Pair programme for prostate cancer patients in the local context of the Loire department. Our primary objective and hypothesis will be related to feasibility outcome and will be to determine adherence to the Acti-Pair programme: the programme will be feasible if 60% of patients reach at least 60% of 1-h session of adapted physical activity (APA) as the minimum weekly threshold over the 3 months of intervention.

Secondary objectives will be to assess the potential effectiveness of the Acti-Pair program by measuring PA levels, quality of life, and implementation outcomes to inform a larger trial.

The purpose of this article is to describe the protocol of this study, following the SPIRIT reporting guidelines [35].

## Methods and analysis

### Study design

This is a pre-post design pilot study using a mixed quantitative and qualitative methodology (*ClinicalTrials.gov**identifier: NCT03866785*). This French pilot study will be performed in cancer centres of Loire district and will be comprised of three successive stages: (1) diagnosis of the target population, (2) recruitment and training of peers, and (3) implementation of this intervention in the Loire department (Fig. 1).

**Fig. 1 Fig1:**
[figure not shown]
Study progress

For these stages, eligible adult patients will be consecutively included after their follow-up consultation with their oncologist or urologist.In the first stage, the aim will be to identify the context of PA management and all the factors that facilitate the patient’s involvement in a more active lifestyle. It will be explored through one-on-one interviews.In the second stage, peers will be trained to acquire the knowledge and skills to perform motivational follow-up of patients.In the third stage, eligible patients will be mentored by peers. This stage will evaluate the reach and efficacy of the peer intervention by using before and after comparisons. This stage will be conducted with a sports and health platform of Loire department. This platform, labelled Sport-Health House in January 2020 by the French Ministry of Sports, is involved in a process of promoting clubs/associations offering a diversity of PAs adapted to (new) sedentary practitioners regardless of their age, level and form. This helps to improve the readability of health sport offers in the Loire department.

### Selection of participants

Patients and peers will be selected via two main hospitals in the Loire department treating patients with prostate cancer: the Lucien Neuwirth Cancerology Institute and the urology department of the St-Etienne University Hospital.

### Patients

The study will include consecutively adult (aged 18 years or older) patients with prostate cancer diagnosed at least one year ago and longer in the process of therapy. Individuals will be excluded from study participation if they are treated with hormone therapy and have cardiac or respiratory conditions contraindicating PA.

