### Peers

Peers will be eligible and will have to meet the same inclusion criteria as patients, but they will also have to change their PA and sedentary behaviour permanently for at least 1 year. They will be physically active according to the WHO recommendations (150 min of MVPA per week).

The study will be conducted in accordance with the Declaration of Helsinki. Prior to starting the experiment, informed oral and written consents will be obtained from all participants. The protocol has been approved by the institutional review board (CPP Sud-Est I, France).

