### Sample size

This is a feasibility study, so we will follow the general rule of thumb is to take 30 patients to estimate the (PA) observance for the target population [36]. We have chosen to include 10 peers and therefore 30 patients so that each peer follows a maximum of 3 patients. Intervention will concern 2 profiles according to the type of initial prostate cancer: (1) localised prostate cancer and locally advanced prostate cancer and (2) metastatic and/or resistant to castration and chemotherapy.

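### The single exclusion sentence leaves men with a contraindication to physical activity eligible if read literally, and conflicts with planned profile 2 if read as two exclusions

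*Protocol article*

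**What the plan says.** Three places in the Methods of the protocol article define who takes part.

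- **Patients.** Adults with prostate cancer are included consecutively if they were "diagnosed at least one year ago and longer in the process of therapy". The only exclusion rule, "Individuals will be excluded from study participation if they are treated with hormone therapy and have cardiac or respiratory conditions contraindicating PA", is this one sentence.
- **Peers.** Mentor eligibility is tied to that of the men they support: "Peers will be eligible and will have to meet the same inclusion criteria as patients". They must also have made a lasting change in their activity.
- **Sample size.** "We have chosen to include 10 peers and therefore 30 patients so that each peer follows a maximum of 3 patients". The section then defines the target population: "Intervention will concern 2 profiles according to the type of initial prostate cancer". Profile 1 is localised and locally advanced disease. Profile 2 is "2) metastatic and/or resistant to castration and chemotherapy".

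The feasibility criterion at the end of the Background is pooled over all patients: the programme counts as feasible if 60% of them reach the session threshold over the 3 months.

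**The concern.** The exclusion sentence joins two different things with one conjunction: a cancer treatment, and a heart or lung condition that the protocol itself says rules out PA. No other part of the article states either exclusion separately or says how the sentence is to be read. Each reading causes a problem. One leaves a gap in a safety exclusion, in a study whose intervention is PA. The other removes patients from a population that the Sample size section says the intervention will cover.

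The inclusion sentence does not help. Its therapy-status phrase may have lost a word (no longer on therapy) or may mean on therapy for a longer time. These select opposite groups.

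At stake are who is enrolled, whether a safety exclusion applies to everyone it should, and which population the 60% result describes.

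**Working it through.** **Stated figure.** 10 peers × 3 patients per peer = 30 patients. This reproduces the planned number, and nothing below changes it. The question is which patients make up the 30.

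**Step 1: the exclusion sentence under each reading.** Let H be treatment with hormone therapy and C a cardiac or respiratory condition contraindicating PA.

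| H | C | Both required (literal) | Two separate exclusions |
|---|---|---|---|
| no | no | eligible | eligible |
| no | yes | **eligible** | excluded |
| yes | no | eligible | **excluded** |
| yes | yes | excluded | excluded |

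The readings differ in the two middle rows, and each bold entry is a problem:

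- *No hormone therapy, contraindication present.* Under the literal reading this man enters a programme that suggests at least 1 hour of moderate-to-vigorous activity (3-month intervention section).
- *Hormone therapy, no contraindication.* Under the separate reading this man is out, whatever his profile.

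**Step 2: the separate reading against the Sample size section.** Profile 2 includes disease resistant to castration. In its ordinary meaning that is disease that has progressed under castration, commonly hormonal treatment. A rule that bars hormone-treated men therefore works against a profile the intervention is said to concern. Under the literal reading the exclusion sentence does not conflict with profile 2.

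**Step 3: size of the loss.** The article gives neither the number expected in profile 2 nor the share on hormone therapy. Both are assumed here, for illustration only. With n₂ men in profile 2 and share s on hormone therapy, the number left is n₂ × (1 − s).

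| n₂ | s = 50% | s = 80% | s = 100% |
|---|---|---|---|
| 10 | 5 | 2 | 0 |
| 15 | 7.5 | 3 | 0 |
| 20 | 10 | 4 | 0 |

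The range is 0 to 10. It shows how strongly the answer depends on a figure the article does not give.

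**Step 4: the inclusion phrase.** If it means no longer on therapy, men with advanced disease who are still being treated fail the inclusion criterion too, which adds to the conflict with profile 2. If it means on therapy for longer, it selects men under treatment. The text does not decide between the two.

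**Step 5: the pooled criterion.** 60% of 30 is 0.60 × 30 = 18 patients. If profile 1 supplied at least 18 of the 30 (profile 2 at most 30 − 18 = 12), the criterion could be met by profile 1 alone. The pooled figure would not show this.

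**The case against.** The strongest reply is that this is a condensed article and that an ordinary reader would take the sentence as a list of two exclusions. On that view the safety gap comes from a strained reading. There are also checks along the way: inclusion follows a consultation with the oncologist or urologist, the attending physician prescribes the activity, and an adapted-physical-activity professional tests each patient beforehand, including a 6-minute walk. Much of this is fair. The list reading is the likelier one, and the checks could expose a contraindication. But none of them is stated as an eligibility rule, and the list reading is the one that conflicts with profile 2. Nor is this a complaint about missing detail, since both passages are stated.

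It is also fair that profiles are assigned by initial cancer type and that profile 2 is wider than castration resistance. Some of its patients may be off hormone therapy. No passage promises a conclusion for each profile, and the Strengths and limitations section already admits the small sample.

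A reader might infer more than the article supports:

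- *That profile 2 would be all but empty.* The article gives no share on hormone therapy; the assumed shares leave anything from 0 to 10.
- *That the exclusion sentence contradicts profile 2 on either reading.* It does so only when read as two exclusions.
- *That profile 2 patients would lack a matching peer, because matching uses similarity of cancer treatment.* The Peers section carries over only the inclusion criteria. No single reading admits profile 2 patients while barring profile 2 peers.
- *That the two hospitals will enrol different populations.* They would work from the full protocol, which is not shown.

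**Conclusion.** The eligibility wording is defective on both readings. Read literally, it leaves eligible a man with a condition contraindicating PA, provided he is not on hormone therapy; this follows from the wording alone. Read as two exclusions, it conflicts with profile 2; this rests on the ordinary meaning of castration resistance. The loss to profile 2 is unknown, and 0 to 10 patients remaining is an illustration under assumed shares. The garbled therapy-status phrase is a further ambiguity and, if it means no longer on therapy, adds to the conflict. The planned 30 patients and the 60% criterion stand as arithmetic. What is unsettled is the population they describe.

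**What to change.** The sponsor should reconcile the Patients and Sample size sections. This review takes no position on which clinical rule is right.

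1. State whether hormone therapy and conditions contraindicating PA exclude a patient separately or only jointly.
2. State the therapy-status criterion so that it has one meaning, for patients and for peers, and say whether the exclusions also apply to peers.
3. Either keep profile 2 with eligibility rules that admit it, or remove it from the Sample size section and limit the feasibility conclusion to the population actually eligible.
4. If both profiles stay, describe adherence by profile beside the pooled 60% criterion, as description only.

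The cost is an amendment to the wording and possibly a narrower stated population. Description by profile uses data already collected and needs no more patients.

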### Peers

Peers will be eligible and will have to meet the same inclusion criteria as patients, but they will also have to change their PA and sedentary behaviour permanently for at least 1 year. They will be physically active according to the WHO recommendations (150 min of MVPA per week).

The study will be conducted in accordance with the Declaration of Helsinki. Prior to starting the experiment, informed oral and written consents will be obtained from all participants. The protocol has been approved by the institutional review board (CPP Sud-Est I, France).

### Sample size

This is a feasibility study, so we will follow the general rule of thumb is to take 30 patients to estimate the (PA) observance for the target population [36]. We have chosen to include 10 peers and therefore 30 patients so that each peer follows a maximum of 3 patients. Intervention will concern 2 profiles according to the type of initial prostate cancer: (1) localised prostate cancer and locally advanced prostate cancer and (2) metastatic and/or resistant to castration and chemotherapy.

### The intervention: the Acti-Pair program

Intervention elements will be described using the Template for Intervention Description and Replication (TIDieR) checklist.

The Acti-Pair program proposes a combination of 3 intervention strategies, the aim of which is to initiate and maintain regular PA in prostate cancer patients:Peer coaching (patient suffering from the same pathology and meeting the WHO recommendations for PA practice), which will provide motivational follow-upThe realisation of a personalized and realistic PA project via the PA platform systems Support by health professionals (attending physician) via the prescription of PA.

### Diagnosis of the obstacles and levers to engage in a PA practice

Semi-structured interviews will be conducted by two sociologists specialising in APA, health, and ageing using common interview grids. They will be preferably conducted face-to-face and recorded using a dictaphone. They will be supported by a Master 2 trainee in public health for the processing of qualitative data (interviews, integral transcription, data analysis). Thirty interviews will be conducted until data saturation.

This comprehensive qualitative study will assess the following: (1) cancer disease and context/environment of subjects, (2) PA recommendations, representations and sports experience, (3) brakes and levers to resumption of PA following diagnosis of cancer; and (4) lifestyle changes since cancer diagnosis with multiple temporalities (future perspectives) and impact of the practice on the overall management of the disease (see supplementary data).

The goal of this diagnosis will be to have a better understanding of levers and obstacles of the target population about their PA practice.

### Recruitment and training of peers

The next phase will be the recruitment of peers. We have chosen to recruit them in the same centres as the target population in order to maximise the chances of having a similar geographical proximity and environment. The main role of peers will be to ensure motivational follow-up of patients in their PA project so that they initiate and/or maintain a regular and sustainable PA.

The peer patient's activities will be to (1) communicate with patients on a regular basis, (2) attend AP sessions, and (3) provide personalised assistance to each patient in order to help them to overcome obstacles in the realisation of the PA personalised project. Mentoring will be focussed on building a supportive relationship with patients, assessing motivational readiness, monitoring PA, identifying health concerns, and identifying and problem-solving barriers to PA, as realised in Pinto’s study [31].

Peer mentors will be trained to enable their acquisition of the knowledge and skills required to accomplish the motivational follow-up of patients. In particular, the objective of this training programme will be the acquisition of the following: (1) skills in PA counselling techniques (empathy, active listening) (imparted by a sports psychologist); (2) knowledge of functional signs or symptoms that might indicate a medical problem in order to ensure patient safety (imparted by a sports physician); and (3) knowledge required to determine heart rate and perceived effort rate in order to ensure an appropriate level of effort (imparted by an adapted physical activity professional, APA).

A qualitative interview will also be conducted to determine the obstacles and levers of the peer’s role before and after the intervention.

